| **6. Materials and Methods** (that could best achieve the study objectives)  **6.1 Study area/setting** (description of the area or setting where the study will be conducted)  The study will be carried out in two villages in eastern Sudan. These villages have relatively stable conditions and no modifications in the applied control measures are expected. They are far from each other and matched for malaria burden, environmental factors and control measures.  The whole area is characterized by seasonal malaria transmission. The season is confined to three months of the year, October – December. The main malaria parasite is *P. falciparum* and the main mosquito vector is *Anopheles arabiensis*10. Subpatent parasitaemias persist in some individuals throughout the dry season, with re-appearance of clinical symptoms in the malaria season associated with reinfection11.  **6.2 Study subjects** (eligibility and exclusion criteria for the study subjects)  The whole residents of the two villages will be recruited into the study. The following ones will be excluded from drug testing :   - pregnant women - children < 3 year old - history of allergy to sulpha drugs - infection with *Plasmodium* species other than *falciparum*   6.3 Combination Therapy:  The antimalarial drug combinations would be: Artesunate (AS) + Sulphadoxine Pyrimethamine (S/P) + primaquine (single dose of 0.75 mg of base/kg body weight) for one group and AS + S/P for the other. These are intended to treat malaria cases, sub-patent parasitaemia and gametocyte carriage. AS and S/P are blood schizontocidal drugs active against *P. falciparum* and gametocytocidal against developing gametocytes of *P. falciparum*. The addition of premaquine is expected to clear mature gametocytes.    6.4 Study design  A community-based intervention study will be conducted in the two villages. The study will start by a baseline evaluation of malaria morbidity and mortality during the transmission season of 2003.  A cross-sectional clinical, parasitological and molecular survey will be carried out during the dry season of 2004. Villagers will be screened for malaria parasite by microscopy. Samples detected negatives by blood films will be screened by conventional nested PCR *Pfs25* primers for detection of sub-patent parasiteamia. Blood will be collected from individuals detected positive by PCR for detection of gametocyte using the RT-PCR technique.  A treatment trial will then be carried out on malaria cases and asymptomatic carriers at the end of the dry season to test the efficacy of two combinations of antimalarial drugs.They will be followedup on days 3, 7 and 14 to confirm the clearance of *P. falciparum*  sub-patent parasitaemia and gametocyte carriage.  The impact of treating sub-patent parasitaemia and gametocyte reservoir on malaria morbidity and mortality will then be evaluated by carrying out a post-intervention survey in the two villages during the next transmission season.  **6.5 Sample sizes**  **6.5.1 Sample size for detection of parasite positive individuals during the dry season:**  The prevalence of sub-patent parasitemia during the dry season is expected to be about 15%. Therefore, the whole two villages will be screened during the dry season for detection of all positives including microscopical cases and subpatent parasitaemia to give the sample size needed for treatment trial.  **6.5.2 Sample size for evaluation of the efficacy of the two combinations**  A trial with 55 subjects on each arm would have 90% power (using a significance level of 0.05) to detect a difference between treatment groups if gametocyte prevalence detected by RT-PCR after treatment is 20% or more on day 3 in AS/SP combination and 5% or less in AS/SP + PQ, allowing for 10% loss to follow up. From earlier surveys the prevalence of sub-patent parasitaemia in the dry season was expected to be about 15% therefore 650 residents of all age groups had to be screened |

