|  |
| **6.5.3 Sample size for detection of the impact of treatment on malaria morbidity and mortality**  Based on the previous records the prevalence in the two villages is expected to be around 10%. Therefore, 216 residents from each village, out of the total of 500, will be examined to detect prevalence between 5 - 15 % at 5% level of significance with a design effect of 2.  The sample sizes were calculated using Epi-Info 2002 computer programme.  6.6. Sampling technique and randomization  Persons who were positive by PCR in the dry season will be enrolled in the study for measuring the efficacy of each combination. The list of eligible participants will be sorted according to village and age, to achieve an implicit stratification. The allocations for this ordered list will be generated using restricted randomization with a block size of 12 in Stata version 7 (Statacorp, Texas)  Simple random sampling technique will be used for the selection of the sample size needed for detecting the impact of the treatment on malaria morbidity.  6.7. Data Collection methods, instruments used, measurements  6.7.1.Describe the instruments used for data collection (questionnaire,observation recording form, etc..), studied variables included in these instruments, and methods used to test for the validity and reliability of the instrument.   - Clinical data will be collected by a medical doctor using a questionnaire. - Thin and thick blood films will be collected on slides by finger brick - A parallel drop of blood will be collected on filter paper from the same finger brick for screening by conventional nested PCR technique. - Microvet tubes will be used to collect 150 ul of blood by finger brick from PCR positive individuals only. Samples will be used for detection of subpatent gametocytes by RT-PCR.     6.7.2.Techniques used should be briefly described and referenced  Thin and thick blood films will be stained and used for species identification and parasite density estimation13.  **Detection of low level *P. falciparum* infection during the dry season**  *P. falciparum* DNA will be extracted from filter papers of microscopically negative blood samples14.  Nested PCR will then be used to detect low level *P. falciparum* infections that prevail during the dry season15. Principal genes to be detected are *Pfs*25 and *Pfg*377, which encode gametocyte specific proteins. Results will then be visualized using gel electrophoresis. Detection of gametocytes using RT-PCR RT-PCR method will be used for detection of sub-patent gametocytemia during the dry season16, 17. Briefly, blood samples collected for RNA isolation and RT-PCR of *Pfs25* and *Pfg377* will first be left at room temperature for 30 minutes, to allow exflagellation and microgamete formation. The plasma and the buffy coat will be removed and the red blood cells stored at -70°C. Total RNA will be isolated using RNA isolation kits. RT-PCR of RNA will then be carried out.   - - 1. **Study definitions (eg case definition) should be mentioned.**   Clinical malaria includes those with microscopically diagnosed *P. falciparum* and clinical symptoms.  Sub-patent parasitaemia includes those detected positive by PCR  Gametocyte reservoirs include those detected positive by the RT-PCR.  **6.8.Data Management and Statistical Analysis**  (Describe the overall plan and tests used for data analysis and statistical package used)  The efficiency of the two treatment regimens will be assessed by comparing the proportions detected positive for asymptomatic infections before and after treatment. Comparison will be done using chi-square test and the significance of the results will be measured by the *P-value*.  Malaria prevalence and percent of mortality will be determined from data collected during the transmission season survey. They will be used for evaluation of the intervention by comparing them between the two villages and with data of the previous transmission season for every village. Comparison will also be done by chi-square test.  The data will be analyzed using SPSS (Statistical Package for Social Science) version 10. |

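### Section 6.8 names only an unadjusted chi-square and specifies no between-arm day-3 comparison that uses the baseline RT-PCR gametocyte status; adjusting would be cheap, but its gain depends on how well that status predicts

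*Protocol*

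**What the plan says.** **Test.** Protocol section 6.8 assesses efficacy by proportions positive for asymptomatic infection before and after treatment, and then states: "Comparison will be done using chi-square test". No stratum or covariate is named.

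**Outcome used for sizing.** Section 6.5.2 plans on "gametocyte prevalence detected by RT-PCR after treatment is 20% or more on day 3 in AS/SP combination" and "5% or less in AS/SP + PQ", with 55 per arm, 90% power, a 0.05 level and 10% loss.

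**Baseline status.** Section 6.4, describing the dry-season survey before the treatment trial: "Blood will be collected from individuals detected positive by PCR for detection of gametocyte using the RT-PCR technique". Section 6.7.1 limits this blood sample to PCR-positive people.

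**Entry and allocation.** Section 6.6 enrols people who were PCR-positive in the dry season; gametocyte carriage is not required. The allocation list is "sorted according to village and age, to achieve an implicit stratification", with blocks of 12.

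**Timing.** The timetable in section 12 puts RT-PCR sampling in month 5, a pre-transmission survey in month 7, and treatment and drug testing in months 7 to 9.

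**The concern.** The sized outcome is RT-PCR gametocyte positivity on day 3. The same marker, measured by the same assay before treatment, is the natural candidate predictor. If many enrolled people carry no gametocytes at baseline, they add few day-3 positives in either arm, and most of the information on the drug contrast lies among the carriers. A crude comparison pools the two groups. The allocation list is ordered by village and age but not by carrier status, so only chance balances carriers between the arms.

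The before-and-after wording does not fill this gap. It concerns infection proportions, and it does not set out a between-arm day-3 contrast conditional on baseline gametocyte status. At stake are precision and power in a small trial, and a main analysis that is not tied to the outcome in section 6.5.2.

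**Working it through.** **1. Inputs from the protocol.** 55 per arm; 10% loss, so 55 × 0.9 = 49.5, taken as 50 evaluable; day-3 prevalence 20% v 5%; level 0.05. Sidedness is not stated and two-sided is assumed.

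**2. The plan's own figure.** The mean rate is 0.125. The pooled-variance formula is

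n = [1.96·√(2 × 0.125 × 0.875) + 1.2816·√(0.20 × 0.80 + 0.05 × 0.95)]² / 0.15² = (0.9167 + 0.5838)² / 0.0225 = 100.1,

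so 101 evaluable per arm. The stated 55 with 90% power is not reproduced. At 50 per arm the same formula gives Φ[(0.15·√50 − 0.9167)/0.4555] = Φ(0.316) = 62%. Exact binomial enumeration of the Pearson test gives 66%, which is the crude reference below.

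**3. Assumptions not in the protocol.** Carrier prevalence q and day-3 positivity in non-carriers, pₙ. Holding each arm's overall rate p fixed, the carrier rate is (p − (1 − q)·pₙ)/q. With q = 25% and pₙ = 2% in AS/SP: (0.20 − 0.75 × 0.02)/0.25 = 0.74, a carrier to non-carrier risk ratio of 0.74/0.02 = 37. With q = 50%: (0.20 − 0.50 × 0.02)/0.50 = 0.38, a ratio of 19.

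**4. Stratified test.** In stratum s, with a positives among n₁ in AS/SP, n₂ in the other arm, t positives in all and N = n₁ + n₂, the statistic is (Σ[a − n₁t/N])² / Σ[n₁n₂t(N − t)/(N²(N − 1))], referred to 3.84.

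**5. Simulated power, 50 per arm, crude about 66% throughout (at least 20,000 trials per scenario).**

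| Day-3 positivity in non-carriers (AS/SP v AS/SP + PQ) | 25% carriers | 50% carriers | 75% carriers |
|---|---|---|---|
| 0% v 0% | 87% | 71% | 67% |
| 2% v 0.5% | 82% | 70% | 66% |
| 5% v 1.25% | 76% | 68% | 66% |
| 10% v 2.5% | 69% | 66% | 65% |
| Risk ratio only 1 to 2 | 64-65% | 64-65% | 64-65% |

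Type I error of the stratified test stays at about 5%.

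**6. Outdated status.** Month 5 to months 7-9 is a gap of about 2 to 4 months. Taking the 2% v 0.5% row and supposing that 10% of statuses have changed, power is 74% at 25% carriers and 67% at 50%. If 20% have changed, it is 69% and 66%.

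**7. Village and age.** Stratifying by village × age alone gives 65-67%, a change of about −1 to +0.5 points, for age risk ratios of 1 to 3 and village risk ratios of 1 to 1.5. All three factors make 8 strata for 50 × 0.20 + 50 × 0.05 = 12.5 expected positives. Power is then 63-73%, with a loss of 3-4 points when baseline status predicts weakly.

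**8. Chance imbalance.** With 30% carriers, the SD of the between-arm difference in carriers is √(2 × 0.3 × 0.7/50) = 0.092, and a gap of 10 points or more occurs in roughly 3 trials in 10. With AS/SP rates of (0.20 − 0.70 × 0.02)/0.30 = 62% in carriers and 2% in non-carriers, a 10-point gap moves the crude difference by 0.10 × (0.62 − 0.02) = 6 points, against a planned 15.

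**The case against.** **The crude test is valid.** After blocked randomisation, chance imbalance in carriers is already covered by the type I error rate and causes no systematic bias. This stands: the issue is efficiency, and a reader who inferred a biased or invalid test would go too far. Covariate adjustment is also often left to an analysis plan, and one may exist here. But the protocol does fix a test, and fixes it without tying it to the day-3 contrast.

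**The gain may be nil.** The large gains need few carriers and risk ratios of 19 to 37 or more. With non-carriers at 10% v 2.5%, the change is about −1 to +3 points. If 20% of statuses have changed by the time of treatment, it is 0 to +3 points at 25-50% carriers. This also stands, so a reader should not infer power for free.

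**Baseline data may be incomplete.** Section 6.4 places malaria cases in the treatment trial, but nested PCR is run on film-negative samples and RT-PCR blood is taken from PCR-positives only. Film-positive cases, if enrolled, have no planned baseline RT-PCR value. It cannot be assumed that every participant has one.

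**Village and age.** One might infer that leaving them out also costs power. The calculations do not support that, and section 6.1 describes the villages as matched for malaria burden. The case for including them is consistency with the allocation.

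**Larger faults exist.** The sample size does not deliver 90% power, and adjustment does not mend that in any scenario tried at 50 per arm.

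**Conclusion.** The point holds as a low-cost improvement of uncertain size. Section 6.8 should specify a between-arm day-3 comparison that uses baseline gametocyte status, because the design collects it and entry does not require carriage.

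Against a crude power of about 66%, the stratified analysis ranges from about 64-65% to 82-87%. The lower end applies if the status predicts weakly, is so outdated that it no longer predicts, or nearly everyone is a carrier. The upper end needs about 25% carriers who supply nearly all day-3 positives. The downside is about 1-2 points. These figures assume a two-sided 5% test, 50 evaluable per arm and the plan's 20% v 5%; carrier prevalence and prognostic strength are assumed throughout. The documents do not support a claim that the gain is certain or that village and age add power.

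**What to change.** In section 6.8:

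- Make the main efficacy analysis a between-arm comparison of day-3 RT-PCR gametocyte prevalence by Mantel-Haenszel, stratified by baseline RT-PCR gametocyte status, with a 95% CI.
- State which pre-treatment sample defines baseline: the month-5 sample, or a later one if the month-7 survey repeats RT-PCR.
- Put participants without a baseline value, such as film-positive cases, in a stratum of their own.
- Keep the crude chi-square as a supplement.
- Use village and age as randomisation factors in a sensitivity analysis only, to avoid sparse strata, and claim no gain in power from them.

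The cost is wording in section 6.8 and a few more lines of analysis. With the month-5 sample, no extra participants, visits or assays are needed. A fresh sample at treatment would make the covariate more current, but would add RT-PCR work unless it is already planned. The shortfall against 90% power needs its own correction in section 6.5.2.

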
| 1. Implications of study results on disease control    1. Expected results and potential contribution of the project to the relevant control programme   It is expected that by the end of this study the suitable and highly effective combination therapy of antimalarial drugs will be identified. The strategy of treating sub-patent parasiaetimia and gametocyte carriage during the dry season is expected to have great impact in malaria morbidity and mortality in the intervention villages during the transmission season. If the expected results are achieved, this strategy of treatment during the dry season with the identified drugs will be recommended to be incorporated into the national malaria control programme of the Ministry of Health for controlling malaria epidemics in areas of marked seasonal transmission.   - 1. Mechanisms to ensure implementation of research results in the health policy of the concerned control programme of the Ministry of Health - A community physician from Malaria, Schistosomiasis and Leishmaniasis Control programme, Federal Ministry of Health(Deputy Director),is co-investigator in the project. He will be in close contact with the progress of the project and its activities and will be aware by the results. - Copies of the progress reports and the final report will be sent to the Control Prgramme. - Formal meeting can be arranged with the staff of the control programme to discuss the findings of the project and the possibility of implementing them. |
| --- |
| 1. Areas of Integration of Research Activities (if applicable)   The project integrates very well with the activities of a national malaria project (SUD 06/21) receiving TC support from the International Atomic Energy Agency (IAEA). This project will benefit from its field and laboratory facilities. [name] [name], U. of Edinburgh, will supervise the RT-PCR part and we will use the field station in Gadarief rent to his MRC malaria project in the area. [name], Medical statistician in the MRC laboratories in the Gambia, greatly helped in the design and will help in statistical analysis and publication of the work. |

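### Section 6.8 judges the regimens by the P-value of a before/after change in people enrolled because they are positive; this neither measures clearance nor compares the two regimens

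*Protocol*

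**What the plan says.** Four places in the protocol bear on this.

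- **6.8, Data Management and Statistical Analysis.** The regimens are assessed by "comparing the proportions detected positive for asymptomatic infections before and after treatment". The next sentence gives the yardstick: "Comparison will be done using chi-square test and the significance of the results will be measured by the" P-value. For efficacy, this is the only comparison described.
- **6.6, Sampling technique and randomization.** "Persons who were positive by PCR in the dry season will be enrolled in the study" for measuring efficacy, and the eligible list is then randomised to the two regimens.
- **6.5.2, sample size for efficacy.** The calculation rests on a between-arm contrast at one time point: "20% or more on day 3 in AS/SP combination and 5% or less in AS/SP + PQ", measured by RT-PCR for gametocytes.
- **5.1, and the section on implications for disease control.** The aim is to find the appropriate drug. The implications section expects that "the suitable and highly effective combination therapy of antimalarial drugs will be identified".

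**The concern.** The test in 6.8 asks whether positivity fell after treatment. The trial asks two other questions: how completely each regimen clears infection, and how much primaquine adds to artesunate plus SP.

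Because enrolment requires a positive PCR, the before proportion is fixed at 100% and can only stay or fall. A test against that starting point rejects easily and does so in each arm separately. Two significant before/after results leave the choice of regimen where it was, and randomisation, the strongest feature of the design, goes unused. If all goes well, the findings are to be recommended to the national control programme, so the analysis should answer the question the trial was built for.

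**Working it through.** **Inputs.** 55 per arm (6.5.2), "allowing for 10% loss to follow up": 55 × 0.9 = 49.5, so about 50 evaluable. Baseline PCR positivity is 100% (from 6.6). Planning rates on day 3 are 20% and 5% (6.5.2). Two-sided 5% level (sidedness is not stated; two-sided assumed).

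**The plan's own figure.** It states that "A trial with 55 subjects on each arm would have 90% power (using a significance level of 0.05") for 20% vs 5%. With pooled variance under the null, n per arm = [1.960·√(2 × 0.125 × 0.875) + 1.282·√(0.2 × 0.8 + 0.05 × 0.95)]² / 0.15² = 100.06, so 101 evaluable. The 55 is not reproduced; power with 50 evaluable is about 62%. That is a separate defect and is not counted here. The calculation matters on this point because it shows that the trial was sized on a between-arm difference.

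**What the before/after test needs.** Compare n of n positive before with n − k of n after, where k is the number cleared.

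- Pearson: χ² = 2nk / (2n − k)
- Yates: χ² = 2n(k − 1)² / [k(2n − k)]
- Exact McNemar, where every change is from positive to negative: P = 2 × (½)^k

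With n = 50:

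| Cleared | Pearson χ² (P) | Yates χ² (P) | Exact McNemar P |
|---|---|---|---|
| 3 (6%) | 3.09 (0.079) | 1.37 (0.241) | 0.250 |
| 4 (8%) | 4.17 (0.041) | 2.34 (0.126) | 0.125 |
| 5 (10%) | 5.26 (0.022) | 3.37 (0.066) | 0.063 |
| 6 (12%) | 6.38 (0.012) | 4.43 (0.035) | 0.031 |

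Significance starts at 4 of 50 by uncorrected Pearson and at 6 of 50 by the other two. McNemar suits the data best, because the same people are measured twice. For 4 of 50 cleared, the exact 95% interval for the proportion cleared is 2.2% to 19.2%: significant by Pearson, and plainly poor clearance.

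**How often that happens.** The protocol gives no expected PCR clearance, so a range is assumed. The chance of at least 6 of 50 cleared is binomial: 38% if true clearance is 10%, 95% if 20%, and 99.9% if 30%. For any regimen worth considering, significance in each arm is close to certain.

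**What the between-arm interval adds.** Suppose 5/50 and 2/50 are gametocyte-positive on day 3. Pearson P = 0.24. The Wilson limits are 4.3% to 21.4% and 1.1% to 13.5%. Newcombe limits for the 6-point difference are:

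- lower: 0.06 − √[(0.100 − 0.043)² + (0.135 − 0.040)²] = −5.0 points
- upper: 0.06 + √[(0.214 − 0.100)² + (0.040 − 0.011)²] = 17.7 points

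The interval runs from slight harm to a sizeable benefit. The P-value alone does not show this.

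**The case against.** Several objections have force.

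- **Intervals and thresholds are often left to an SAP, which is not shown here.** This stands for anything that is merely absent. It does not cover the sentence that 6.8 does contain, which fixes the comparison as before/after and the measure as a P-value.
- **The proportions will be seen.** True. A fall from 50/50 to 46/50 would be visible as 92% still positive. A reader might infer that the trial cannot identify an effective regimen; that goes too far. The stated analysis gives no basis for the choice, but the data would.
- **No decision rule is written.** Also true. A reader might infer that P below 0.05 is to be taken as highly effective, or P above 0.05 as no benefit from primaquine. The protocol says neither, and its recommendation to the control programme is conditional on the expected results being achieved.
- **The 8% is fragile.** It needs the uncorrected test and the 100% PCR baseline. It does not carry over to gametocytes, whose baseline RT-PCR positivity is not given.
- **A reader might combine easy significance with missed benefit in one test.** These belong to different tests. If both regimens work, each before/after test is strongly significant; only a between-arm test would be non-significant (3/50 vs 2/50 still positive gives P = 0.65). At the planned rates with 50 per arm, a between-arm P above 0.05 would occur in about 34% of trials, but this comes largely from the sample-size shortfall.
- **The wording might be meant to include a between-arm test.** Possibly, given 6.5.2. Then 6.8 should say so.

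**Conclusion.** The point holds as a mismatch between the stated analysis and the trial's question. Followed literally, 6.8 tests a change that becomes significant at 8% to 12% clearance with about 50 per arm, depending on the version of the test, and that neither quantifies clearance nor compares the regimens. The comparison that answers 5.1 is the one used in 6.5.2.

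The 8% to 12% rests on two assumptions: about 50 evaluable per arm, and a before value taken at the PCR screen that determined enrolment. If positivity were measured again just before treatment, the before value could be below 100% and the threshold would shift; the mismatch would remain.

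The documents do not support reading the 15-point planning difference as a margin below which primaquine adds little. It is a superiority assumption, and using it as a margin would be a new choice. Nor is the lack of a numerical bar for high effectiveness a finding here. The change should be made, but the point is moderate in weight.

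**What to change.** Replace the efficacy sentences in 6.8 so that they state:

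1. The efficacy measure is the difference between arms in RT-PCR gametocyte prevalence on day 3, with a 95% confidence interval (Newcombe, for example) and the chi-square P-value for that difference.
2. For each arm, the proportion cleared among those positive before treatment is reported with an exact 95% confidence interval, as a description.
3. A non-significant difference is interpreted from its interval and is not read as showing no benefit.

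This aligns 6.8 with 6.5.2 and uses follow-up that 6.4 already plans. It costs a few lines and no extra samples or visits. The drawback is that an inconclusive comparison will be visibly inconclusive, which is likely enough at the present sample size.

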| --- |
| **5. Objectives of the study:**  **5.1 General objective** (overall objective, one paragraph maximum)  To identify the appropriate drug which can be used for treating *P. falciparum* sub-patent parasitaemia and gametocyte reservoir during the dry season in an area of marked seasonal malaria transmission in eastern Sudan. The ultimate aim is to reduce malaria morbidity and mortality during the transmission season.  **5.2 Specific objectives:** (should cover the details of the general objective)   - To identify individuals with sub-patent parasitaemia during the dry season using nested PCR technique - To identify gametocyte carriers among them using RT-PCR - To carry out a community-based intervention study for testing the efficiency of two drug combinations; Artesunate plus Sulphadoxine Pyrimethamine (S/P) and Artesunate plus Sulphadoxine Pyrimethamine (S/P) plus primaquine in clearing sub-patent parasitaemia and gametocytaemia from carriers at the end of the dry season. - To evaluate the effect of such a strategy on malaria morbidity and mortality during the transmission season.   **5.3 Secondary objectives (optional):** these are subsidiary objectives that could be studied during the course of the project but are not the main objectives of the study.  None |

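### Mortality is a tested outcome in Protocol 5.2, 6.5.3 and 6.8, but no way of ascertaining deaths is described, the sample is sized only for prevalence, and villages of 500 are too small for the chi-square test

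*Protocol*

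**What the plan says.** Section 5.2 lists as a specific objective: "To evaluate the effect of such a strategy on malaria morbidity and mortality during the transmission season". Section 6.4 says this will be evaluated by a post-intervention survey in the two villages during the next transmission season.

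Section 6.5.3 is headed "Sample size for detection of the impact of treatment on malaria morbidity and mortality". Its calculation starts from a prevalence: "Based on the previous records the prevalence in the two villages is expected to be around 10" per cent. It concludes that "216 residents from each village, out of the total of 500, will be examined to detect prevalence between 5 - 15" per cent, "at 5% level of significance with a design effect of 2".

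Section 6.6 describes the purpose of that sample more narrowly: "Simple random sampling technique will be used for the selection of the sample size needed for detecting the impact of the treatment on malaria morbidity". Mortality is not named there.

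Section 6.7 lists the data collection: a questionnaire for clinical data completed by a doctor, blood films, filter paper and blood tubes. The study definitions cover clinical malaria, sub-patent parasitaemia and gametocyte reservoirs.

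Section 6.8 fixes the source for mortality, "Malaria prevalence and percent of mortality will be determined from data collected during the transmission season survey", and applies a chi-square test between villages and against the previous season within each village.

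Section 6.1 puts the season in October to December. The timetable (section 12) marks the 2003 survey in M10 and M11, the post-intervention survey in M11 only, and the final report in M12. The budget (section 13) covers four field surveys of 5 days each.

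**The concern.** The protocol names mortality as an objective and fixes its data source, its comparisons and its test. It gives no procedure for learning that someone has died, no definition of a malaria death and no denominator for the percentage. The sample size section says it covers mortality, but the figure it produces concerns prevalence alone. These are statements in the protocol itself, so they are not details left to a statistical analysis plan.

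At stake is the conclusion on half of one specific objective. The section on implications for disease control expects a large effect on morbidity and mortality and says that, if the expected results are achieved, the strategy will be recommended to the national programme. A mortality comparison with almost no events could be read as support, or as lack of effect, when it carries little information either way. The randomised drug comparison of section 6.5.2 is not affected.

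**Working it through.** **Step 1. Reproduce the 216.** Inputs from 6.5.3: prevalence 0.10, limits 0.05 to 0.15 (so d = 0.05), 5% level (z = 1.96), village size N = 500, design effect 2.

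- Precision sample for one proportion: n0 = z² p(1−p)/d² = 1.96² × 0.10 × 0.90 / 0.05² = 138.3
- Finite population correction: n0/(1 + n0/N) = 138.3/(1 + 138.3/500) = 108.3
- Times the design effect: 108.3 × 2 = 216.7 (or 108 × 2 = 216)

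The stated figure is therefore explained in full as a precision sample for a 10% prevalence. No death rate and no between-group difference enters it.

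**Step 2. What the survey window covers.** If M11 is November, which fits the season and the 2003 survey in M10 and M11, a 5-day visit in that month cannot record deaths that occur later in the season. The 2003 survey spans two marked months and the later one spans one, so the two periods may also differ.

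**Step 3. Deaths needed for significance if all were captured.** Uncorrected chi-square with k deaths against 0 and n per village: X² = (k/n)² / [p(1−p) × 2/n], with p = k/(2n). The critical value is 3.84.

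| Deaths | n = 216 | n = 500 |
|---|---|---|
| 3 against 0 | X² = 3.02 | X² = 3.01 |
| 4 against 0 | X² = 4.04 | X² = 4.02 |

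At least 4 deaths against 0 are needed, which is 4/500 = 0.8% or 4/216 = 1.9% of one village. Fisher's exact test needs 6 against 0.

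**Step 4. Death proportion needed for expected counts of 5.** 5/500 = 1.0% with complete capture; 5/216 = 2.3% in the sample.

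**Step 5. Expected deaths.** The protocol gives no death rate. Assumption: all-cause mortality of 5 to 20 per 1000 per year, evenly spread, with a season of one quarter of a year.

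- Whole village: 500 × 0.005/4 = 0.63 to 500 × 0.020/4 = 2.5
- Sample: 216 × 0.005/4 = 0.27 to 216 × 0.020/4 = 1.08

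Malaria deaths are a subset of these.

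**Step 6. Power with complete capture.** Exact power of the uncorrected chi-square, by enumerating two binomials with 500 per village and an assumed halving between villages:

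| Seasonal death proportions | Expected deaths | Power |
|---|---|---|
| 0.1% vs 0.05% | 0.5 vs 0.25 | 0.1% |
| 0.2% vs 0.1% | 1.0 vs 0.5 | 1.2% |
| 0.5% vs 0.25% | 2.5 vs 1.25 | 7.8% |
| 1% vs 0.5% | 5.0 vs 2.5 | 13% |
| 2% vs 1% | 10 vs 5 | 24% |

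The range in Step 5 corresponds to 0.125% to 0.5% per season, so the last two rows lie beyond it. At 0.5% vs 0.25%, 80% power would need 9,383 residents per village.

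**The case against.** A reader might infer that the survey is bound to record no deaths, because only living people can be examined. The protocol does not support that. Section 6.8 takes mortality from data collected during the survey and does not say that deaths are counted only among those examined. The content of the doctor's questionnaire is not given, the form leaves data collection instruments to annexes that are not at hand, and householders are contacted for consent. A question on deaths in the household would count as data collected during the survey. Nor does 6.6 tie mortality to the 216, since it names morbidity only. What stands is narrower: no ascertainment and no denominator is described.

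Other points have force. The timetable does not name calendar months, so reading M11 as November is an inference. The death rates and the halving are assumptions, and the rates are all-cause while the objective is malaria mortality; that last difference makes the counts smaller. The choice of an exact test for sparse tables could be left to an analysis plan. However, Fisher's test asks for more deaths here, so changing the test would not help. Finally, no passage says that a near-zero mortality would be presented as evidence. That risk is inferred from the policy recommendation the protocol anticipates.

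**Conclusion.** The concern holds in this form. Mortality is a tested outcome for which the protocol describes neither ascertainment nor denominator, and the heading of 6.5.3 claims a sizing that its calculation does not provide. These two statements rest on the text and on Step 1 alone.

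That the test would be uninformative follows from the size of the villages. With complete capture of deaths among 500 residents each, significance needs at least 4 deaths against 0, and expected counts of 5 need 1.0% of residents to die within one season. Under the assumed rates, 0.6 to 2.5 deaths are expected per village-season, and power for a halving is at most about 8%. Better ascertainment alone would not repair the comparison. The conclusion would weaken only if seasonal mortality were well above the assumed range; even 2% against 1% gives 24% power.

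This should be corrected, but it is not critical: the prevalence survey and the drug comparison do not depend on it.

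**What to change.** **Wording changes, at no cost in data:**

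- 6.5.3: delete mortality from the heading, so that it agrees with the calculation and with 6.6.
- 6.8: remove the percentage of mortality from the chi-square comparisons.
- 5.2: state that mortality is not a tested outcome. The sentence in 6.4 should match.

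The sponsor gives up only a mortality claim that the design could not support.

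**If deaths are kept,** report them as descriptive counts and proportions with exact confidence intervals and no test. Use a household question with the same stated recall window in both seasons' surveys, and take all residents of the households asked as the denominator. This adds one question per household. It must be in the baseline survey too, or only the comparison between villages in the second season remains. The intervals will show how little is known: with 0 deaths among 500, the exact 95% upper limit is 1 − 0.025^(1/500) = 0.7%, or about 3.7 deaths.

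**A count over the full season costs more.** It needs contact with households after December. That falls outside the surveys in the timetable, may exceed the four 5-day surveys in the budget, and moves the final report later than M12. A stated shorter recall window avoids this, provided that the report says which part of the season it covers.
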